
### Usual care

The control group is receiving counselling according to care as usual. This care consisted of minimal involvement by the IP and, to a lesser extent, of other OH professionals. In this scenario, the active sickness absence counselling starts at a later time point during the sick leave process. Furthermore, there is minimal referral to external intervention partners and, if referred, it does not occur using the stepped care approach, which is based on the classification category assigned in the intervention group. Finally, early reintegration into primary paid work or enhancing work experience is not the main goal of usual care. We will record the interventions received by the workers in the control group.

### Study design

Participants are allocated to two groups: an intervention group, in which the participants receive the Brainwork Intervention and a control group, in which participants receive usual care (see Figure 2). The study was presented to the Medical Ethics Committee of the Academic Medical Center (AMC), University of Amsterdam. The Medical Ethics Committee declared that the study design did not require comprehensive ethical review, as the Medical Research Involving Human Subjects Act does not apply to this study [29]. Besides the decision of the Medical Ethics Committee, the study has to adhere to Research Code of AMC. This study is listed in the Netherlands Trial Register (NTR) under NTR4190.

**Figure 2 Fig2:**
[figure not shown]
Design of the study.

### Setting

The controlled clinical trial is conducted in collaboration with three front offices of the Dutch SSA across the Netherlands (Hengelo (east), Rotterdam (south-west), Den Bosch (south)), vocational rehabilitation agencies, mental health institutions/professionals and companies that specialised in activating rehabilitation programmes consisting of physical exercise, dealing with coping and lifestyle management.

### Study population

The population in this study consists of unemployed and temporary agency workers and workers with expired fixed-term contracts, who live in the eastern, south-western or southern part of the Netherlands and when sick-listed are the responsibility of the three participating front offices of the Dutch SSA. The inclusion criteria are: (1) being an unemployed or temporary agency worker or worker with an expired fixed-term contract; (2) between 18 and 64 years of age; (3) sick-listed and not expected to RTW within two weeks after reporting sick or contact with the vocational rehabilitation counsellor of the SSA; (4) having psychological problems/complaints as the main reason for a sickness benefit claim; and (5) adequate command of the Dutch language. The exclusion criteria are: (1) recent pregnancy or up to three months after delivery; (2) substance addiction (alcohol, drugs and medicines) as the main reason for a sickness benefit claim; (3) having a severe psychiatric disorder with an expected recovery of more than one year (e.g., hospitalization or day treatment).

### Procedure

#### Recruitment of participants

The sick-listed workers with psychological problems from one of the three participating front offices of the SSA are included in the study if they meet the inclusion criteria. After inclusion in the study, the workers receive a letter from the staff IP of the appropriate SSA front office, on behalf of the investigators. The purpose of this letter is to provide information about the study and to ask for the workers cooperation (informed consent) in completing questionnaires during the study. In addition, the workers also receive an informational flyer containing additional details about the study, a baseline questionnaire, an informed consent form, a refusal form for those not willing to complete the questionnaires, and a return envelope for the baseline questionnaire or refusal form. At follow-up, only the sick-listed workers who signed an informed consent form to fill the questionnaires are approached. Evaluation of the workers’ questionnaires takes place at baseline, and 4, 8 and 12 months after the SSA received the sick report. The questionnaires are sent to the participants’ home addresses.

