### Randomisation

Quasi randomisation is conducted at the participant (workers) level at each of the three participating front offices of the Dutch SSA. Because workers with expired fixed-term contracts are registered later during the sick leave process, the Brainwork Intervention also begins later for this group. Therefore, the sick-listed workers are pre-stratified based on the type of worker (i.e., unemployed and temporary versus expired fixed-term contracts) to ensure equal distribution of the different types of workers in the control and intervention group. Because a blinded allocation is impractical and difficult to set up in the practice of the Dutch SSA, the following allocation scheme is used: the first five sick-listed unemployed and temporary agency workers with psychological problems, as identified by each participating Dutch SSA front office, and who met the inclusion criteria are allocated to the intervention group. The first five workers with expired fixed-term contracts having psychological problems are allocated to the control group. The next five sick-listed unemployed and temporary agency workers having psychological problems are allocated to the control group, while the next five workers with expired fixed-term contracts are allocated to the intervention group and so on. The person who allocated the worker to either control or experimental group is unaware of the type or severity of the psychological problem, or of any other participant characteristics.

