### Data analysis

All statistical analyses will be performed at worker’s level according to the intention-to-treat principle. To check the success of the quasi randomisation procedure similarities in the descriptive statistics will be determined, comparing the baseline measurements of both groups. If necessary, the main analyses will be adjusted for prognostic dissimilarities. For those aspects of the protocol which were fixed for all participants, such as personal attention given by the OH professional to the sick-listed worker through face-to-face contact within five working days after the SSA received the sick report, or timely referral of the worker to the external intervention partner, the protocol deviations will be analyzed. To assess the presence of bias due to protocol deviations, the results of the intention-to-treat analyses will be compared to per-protocol analyses.

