#### Effect evaluation

To assess the effectiveness of the Brainwork Intervention for the primary outcome, a Linear Mixed Models (LMM) analysis of the differences between the average sick leave duration (in days) in the intervention and control group will be performed. Therefore, a model with group as fixed factor and the vocational rehabilitation counsellor of the SSA at a primary hierarchical level and the participants at a secondary hierarchical level (where appropriate) will be built. For all participants who have not returned to work after 1 year of follow-up, the value of 365 days of sickness absence will be imputed.

For the secondary outcomes, excepting costs and benefits, LMM analysis for continuous outcomes and Generalized Linear Mixed Models analysis for dichotomous/ordinal outcomes will be performed. Therefore, a model with group as fixed factor and the vocational rehabilitation counsellor of the SSA at a primary hierarchical level and the participants at a secondary hierarchical level (where appropriate) will be built. In the case of differences in the ratios between the types of workers (unemployed and temporary agency versus expired fixed-term contract) due to attrition, a correction for the differences will be performed by including type of worker as a covariate in the analysis.

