### Methodological considerations

The design of our trial is considered feasible for the assessment of the effectiveness of a RTW intervention and fits well in the daily practice of the Dutch insurance physician. In this pragmatic trial, effectiveness instead of efficacy is studied. This increases the applicability of the intervention and has the advantage that the results will be more in line with daily occupational health practice, resulting in a high external validity [35-38].

The strength of this study is the data collection from a social security database, which contains accurate information on our primary outcome measure, duration of sick leave. Accurate information can be obtained from this database because these data are used for calculating sickness benefit claims. Register-based data, which are used for calculating earnings, are considered to be a gold standard [39-42] and prevent recall bias [40]. As a result, loss of primary outcome data due to the loss of the worker to follow-up is not expected. Thus, this study has a low risk of attrition bias. Deriving primary outcome data from the database also leads to a low risk of detection bias, despite the lack of blinding to the sick-listed workers, OH professionals and the intervention partners that are allocated to the intervention or control group. However, concerning one secondary outcome measure (number of days of paid employment during follow-up), data on RTW are also collected from self-report questionnaires because the Dutch SSA, in many cases, no longer retains data on RTW after sickness benefits have ended. As such, data collection from the database alone might underestimate RTW during the one-year follow-up.

Because the activating approach of our intervention is a well-known concept and described in detail, we expected that the results of this study are generalizable and applicable in other countries.

Results of this study will become available in 2015.

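### Follow-up GHQ-12 and return-to-work self-efficacy exist only for workers who sign a later questionnaire consent, so the unqualified intention-to-treat statement does not hold for them and the low-attrition statement is supported only for register outcomes

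*Protocol article*

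**What the plan says.** All places are in the Protocol article.

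- **Recruitment of participants.** Workers who meet the criteria are included. Then "After inclusion in the study, the workers receive a letter from the staff IP of the appropriate SSA front office". Its purpose is to inform them and "to ask for the workers cooperation (informed consent) in completing questionnaires during the study". The mailing holds the baseline questionnaire, a consent form and "a refusal form for those not willing to complete the questionnaires". For later rounds, "At follow-up, only the sick-listed workers who signed an informed consent form to fill the questionnaires are approached".
- **Study population.** Consent is not among the inclusion criteria.
- **Randomisation.** Workers are allocated in alternating blocks of five as the front office identifies them. The reason given is: "Because a blinded allocation is impractical and difficult to set up in the practice of the Dutch SSA". **Blinding** says that workers and professionals are not blinded.
- **Secondary outcomes and Table 2.** GHQ-12 and return-to-work self-efficacy come from questionnaires alone. Days of paid employment and degree of participation come from questionnaires and the agency's database. The other outcomes come from the database.
- **Data analysis.** Every statistical analysis is to be done "according to the intention-to-treat principle". If baseline comparison shows it to be necessary, the main analyses are adjusted for prognostic differences.
- **Effect evaluation.** For secondary outcomes other than costs and benefits, "LMM analysis for continuous outcomes and Generalized Linear Mixed Models analysis for dichotomous/ordinal outcomes will be performed", with group as fixed factor. Worker type is added as a covariate if attrition shifts its distribution.
- **Methodological considerations.** After an argument about register data for the primary outcome: "Thus, this study has a low risk of attrition bias".

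**The concern.** A worker who refuses the questionnaires stays in the trial and in the register, but has no GHQ-12 or self-efficacy value at follow-up and normally none at baseline. The planned model can include only workers with at least one value. For these outcomes the analysed set is consenting responders, not everyone allocated.

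The design gives a reason why willingness to respond could differ by arm. Brainwork starts with face-to-face contact within five working days of the sick report, is meant to build commitment, and is delivered by teams trained in motivational interviewing. Usual care has minimal involvement and starts later. If those who respond differ between arms in ways related to the outcome, that difference shows up as an effect. The Discussion expects mental-health benefits, and GHQ-12 is the outcome that would bear this out. A reader told that all analyses are intention-to-treat, in a study with low attrition bias, would give that comparison more weight than its design supports.

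**Working it through.** **1. Who has data**

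| Outcome | Source (Table 2) | Held for |
|---|---|---|
| Duration of sick leave; proportion returned; duration from transfer; costs and benefits | Database | All included workers |
| Days of paid employment; degree of participation | Database and questionnaire | Database part: all; questionnaire part: consenting responders |
| GHQ-12; return-to-work self-efficacy | Questionnaire | Consenting responders |

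Methodological considerations adds that the agency often no longer holds return-to-work data once benefits end, so the questionnaire part of paid employment matters.

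**2. What the mixed model can do.** It uses partial follow-up under missing at random. A worker with no value at any time contributes nothing. Covariates can make a responder comparison fair, but only for selection that runs through those covariates.

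**3. Possible size.** The article gives no response rate or correlation, so there is no figure of its own to reproduce on this point. The one usable number is the planned 300 workers, taken as 150 per arm (equal split assumed). Everything else below is assumed.

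Let the outcome have SD 1 and no treatment effect. Let a share r respond, and let rho be the correlation between outcome and willingness to respond. The mean among responders is rho × φ(c)/r, with c the (1 − r) normal quantile. φ(c)/r is 0.798 at r = 0.5, 0.644 at 0.6, 0.497 at 0.7 and 0.350 at 0.8.

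- 70% v 50%, rho 0.3: 0.3 × (0.497 − 0.798) = −0.09 SD. The standard error is √(1/105 + 1/75) = 0.151, treating the responder SD as 1. A two-sided 5% test then rejects in 9.2% of trials.
- 70% v 50%, rho 0.1 and 0.5: −0.03 and −0.15 SD; 5.5% and 16.9%.
- 80% v 50%, rho 0.1, 0.3 and 0.5: −0.05 (−0.045 before rounding), −0.13 and −0.22 SD; 6.1%, 15.0% and 33.1%.
- 60% in both arms, rho 0.3 in one arm and 0 in the other: 0.3 × 0.644 = 0.19 SD; 25%.
- 60% in both arms, rho 0.3 and −0.3: 0.6 × 0.644 = 0.39 SD.
- Same rate and same selection in both arms: 0; 5%.

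**4. Direction, and what register data can correct.** This was simulated with 2 million workers per arm, no true effect, and 65% (Brainwork) v 45% (control) responding. Complaints correlate 0.3 or 0.5 with register sick-leave duration. Where selection acts, the log-odds of response change by 0.5 per SD. Weights were estimated from duration, separately by arm. Differences are Brainwork minus control in SD, with higher meaning more complaints.

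| Response depends on | Unweighted (0.3; 0.5) | Register-weighted (0.3; 0.5) |
|---|---|---|
| Duration, control only | −0.08; −0.13 | below 0.01 in size |
| Duration, same slope in both arms | −0.03; −0.05 | below 0.01 in size |
| Duration, control only, opposite sign | +0.08; +0.13 | below 0.01 in size |
| Complaints themselves, control only | −0.26; −0.26 | −0.24; −0.20 |

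If response in control depends on baseline complaints (baseline to follow-up correlation 0.5), the unadjusted difference is −0.13 SD. With the baseline value as covariate it is within 0.002 of zero.

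**The case against.** **The wording can be read more kindly.** The low-attrition sentence closes an argument about the primary outcome, for which it is reasonable, and the Primary outcome section makes the narrower claim. Intention-to-treat can mean only that workers are analysed in the arm they were allocated to. This stands in part: the low-attrition statement is too broad rather than unfounded. But intention-to-treat is claimed for all analyses, and most of its protection is lost when an unknown share of the allocated workers cannot enter the analysis.

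**There are safeguards.** The plan may adjust for baseline differences and for worker type, and step 4 shows that baseline adjustment can remove bias that runs through the baseline value. This also stands, but both adjustments are conditional, and it is not explicit that the first reaches the questionnaire outcomes.

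**A missing-data method belongs in the analysis plan, which is not shown.** Agreed; its absence is not the point. The point is that the article's own statements do not fit its own data collection. The added analysis is offered because register data on every included worker are already available.

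**The order of events is inferred.** The article does not say outright that allocation precedes the letter, or that a worker knows the arm when signing. The sections on recruitment, randomisation and early contact strongly suggest it. Whatever the order, consent follows inclusion and non-signers are not followed. Refusers are nevertheless approached once, since the baseline mailing goes to every included worker.

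**Conclusion.** The point holds for GHQ-12 and return-to-work self-efficacy, and in part for days of paid employment and degree of participation. Their analysis is of consenting responders, the intention-to-treat statement needs a limit, and the low-attrition statement is supported only for register outcomes.

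Bias is a risk of unknown size and direction. Under the assumed response rates and selection it runs from about 0 to 0.2 SD or more, of either sign. It needs response that is related to the outcome and that acts differently in the two arms.

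Three stronger readings are tempting, and the documents support none of them:

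- That the questionnaire results will favour Brainwork. No response rate or direction of selection is given, and reversing the assumed selection reverses the sign.
- That weighting from the register removes the problem. It does so only if response depends on what the register records; where response depends on complaints themselves, 0.20 to 0.24 SD of 0.26 remains.
- That the main result is compromised. The primary outcome and the other outcomes taken only from the register do not depend on questionnaire consent.

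**What to change.** 1. In Data analysis and Methodological considerations, limit the intention-to-treat and low-attrition statements to register outcomes, and describe the questionnaire analyses as analyses of consenting responders.
2. Report consent and response by arm at baseline, 4, 8 and 12 months, and compare responders with non-responders on register data.
3. Keep the mixed model for questionnaire outcomes, adjusted in every case for worker type and, where one is measured, the baseline value.
4. Add one pre-specified analysis by multiple imputation or inverse-probability-of-response weighting. Build it separately by arm from register data held on all included workers, such as office, worker type, and benefit status and duration. Use these only in the imputation or weight model: benefit status and duration arise after allocation and should not be covariates of the effect.
5. State that this analysis corrects only selection explained by register data.

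The cost is a few sentences, some programming and slightly wider intervals for these outcomes. No new data are needed.

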#### Recruitment and training of occupational health professionals

At each SSA office, an existing team of OH professionals is designated as an intervention team and one as a control group team. An OH professional team consists of insurance physicians, vocational rehabilitation counsellors, labour experts, at least one nurse practitioner and secretaries. Instruction and coaching sessions are held for all of the OH professionals on the intervention team. Members of this team also receive a syllabus with detailed information about the Brainwork Intervention, the protocol, practical summaries, flowcharts, a schedule of actions and the registration forms to aid in the application of this new intervention. Furthermore, team members receive a two-day training in motivational interviewing. The training provides the OH professionals with the motivational interviewing skills necessary to activate the sick-listed workers’ participation in the Brainwork Intervention, to initiate positive behavioural changes and to address resistance to change of the sick-listed workers.

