### Intervention

#### Brainwork Intervention

To optimize the sickness absence counselling of sick-listed workers without an employment contract who have psychological problems, occupational health (OH) professionals of one of the front offices of the Dutch SSA developed the Brainwork Intervention. The intervention is optimized by categorizing the sick-listed workers and targeting social-medical interventions to the specific categories of workers. The core elements of the Brainwork Intervention are: (1) personal attention given by the OH professional to the sick-listed worker through face-to-face contact, within five working days after the SSA received the sick report; (2) classification of the worker based on the severity of the psychological problems, the degree of functional impairments or loss of control and estimated recovery time of the sick-listed worker by the IP (see Table 1); (3) early activation of the worker and provide structure to the worker by formulating explicit goals and timetables for recovery, the early reintegration into primary paid work and if necessary, enhancing work experience or carrying out volunteer work, and an exercise program; (4) referral of the worker to additional specific psychological and/or social interventions such as psychological treatment (e.g., dealing with coping problems or eye movement desensitization and reprocessing (EMDR) for persons with impaired trauma counselling) and debt counselling; (5) facilitating a timely internal work process for the SSA by optimizing the collaboration between the OH professionals involved (IP, vocational rehabilitation counsellor, labour expert, nurse practitioner, secretary); (6) intensive vocational counselling by the SSA; (7) counselling by a vocational rehabilitation agency.

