### Measures

#### Primary outcome

##### Duration of sick leave

The primary outcome measure in this study is duration of sick leave and operationalised as duration of the sickness benefit period (in days) from the first day of reporting sick until the end of the sickness benefit. The sickness benefit ends after a full RTW (e.g., for temporary agency workers) or if the participant is declared fit for work (e.g., for unemployed workers). Data on sickness benefit duration are continuously registered by the SSA and will be acquired from the SSA database six months after inclusion of the last participant and after a one-year follow-up period. Because the SSA registers all the data regarding sickness benefit claims, a loss of data to follow-up with regard to the primary outcome is not expected.

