### Sample size and power analysis

A power analysis was performed to calculate the required number of participants in this study. The mean and standard deviations of the duration of sick leave of all sick-listed workers without an employment contract having psychological problems who registered at the SSA in 2011 were taken as a starting point. Because there are no data available from previous studies on the expected differences, we only calculated how many participants are needed to display any differences in duration of sick leave. The power analysis using program nQuery Advisor showed that 144 participants are needed per group (288 total) to detect a mean difference in duration of sick leave of 40 days. Therefore, we decided to include 300 participants for this study.

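### Each office has one existing team per arm, so pre-existing differences between teams are aliased with the Brainwork effect, and the planned analysis cannot remove a systematic one.

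*Protocol article*

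**What the plan says.** All references are to the protocol article.

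- **Setting**: the trial runs in "three front offices of the Dutch SSA across the Netherlands".
- **Recruitment and training of occupational health professionals**: at each office, "an existing team of OH professionals is designated as an intervention team and one as a control group team". The team is the whole professional chain: "An OH professional team consists of insurance physicians, vocational rehabilitation counsellors, labour experts, at least one nurse practitioner and secretaries". The intervention team is instructed, coached and trained in motivational interviewing. How the two teams were picked is not described.
- **Randomisation**: "Quasi randomisation is conducted at the participant (workers) level at each of the three participating front offices of the Dutch SSA". Blocks of five workers alternate between arms within type of worker. No step allocates teams.
- **Duration of sick leave**: the benefit period, which is the primary outcome, ends at full return to work or "if the participant is declared fit for work".
- **Effect evaluation**: the primary analysis is "a model with group as fixed factor and the vocational rehabilitation counsellor of the SSA at a primary hierarchical level", qualified as applying where appropriate. No team or office term is named.
- **Data analysis**: adjustment for dissimilarities rests on comparing the two groups' baseline measurements.
- **Methodological considerations**: attrition and detection bias are discussed; the pairing of team with arm is not.

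**The concern.** Allocating workers balances workers. It does nothing to balance the teams that handle them. No team is described as serving both arms, so within an office any standing difference in how two teams work falls entirely into the arm contrast.

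The primary outcome is open to such a difference. A benefit can end when a worker is declared fit, and teams may differ in how early they reach that point. The article does not say who makes the declaration. That team members do so is an inference: The Dutch social security system section says an insurance physician usually conducts the counselling, and insurance physicians belong to the teams. If the inference is right, a designated Brainwork team that already closed claims sooner than its neighbour would show shorter sick leave even if Brainwork did nothing. The reverse pattern would hide a real benefit.

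**Working it through.** **1. The aliasing.** Three offices with two teams each give six teams, three per arm. Each team serves one arm, so fixed team terms would be aliased with group. Counsellors sit inside teams and teams inside arms. A counsellor random effect therefore captures within-arm variation between teams in part, but not a shift common to the designated intervention teams. This step needs no assumed figures.

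**2. The SD behind the stated sample size.** The plan states that "144 participants are needed per group (288 total) to detect a mean difference in duration of sick leave of 40 days", without giving SD, alpha or power. Solving n = 2(z_α + z_β)²SD²/Δ² for the SD, with n = 144, Δ = 40 and two-sided 5%:
- 80% power: SD = 40 × √72 / (1.960 + 0.842) = 121 days
- 90% power: SD = 40 × √72 / (1.960 + 1.282) = 105 days

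The stated 144 is thus attainable but cannot be checked independently.

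**3. Further assumptions.** 150 workers per arm (300 planned), 50 per team if offices recruit equally, and a team intraclass correlation (ICC) of 0.01 to 0.05. The article gives no ICC.

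**4. Arm difference caused by teams alone.** Its SD is SD × √(ICC × 2/3).

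| ICC | SD 105 | SD 121 |
|---|---|---|
| 0.01 | 8.5 days | 9.9 days |
| 0.02 | 12.1 days | 14.0 days |
| 0.05 | 19.1 days | 22.1 days |

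For comparison, the worker-level standard error at SD 121 is 121 × √(2/150) = 14.0 days.

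**5. Type I error if clustering is ignored.** The design effect is 1 + 49 × ICC, and the error is 2(1 − Φ(1.96/√DE)).
- ICC 0.01: DE 1.49, error 0.108
- ICC 0.02: DE 1.98, error 0.164
- ICC 0.05: DE 3.45, error 0.291

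**6. Type I error with counsellors as the analysis unit.** This is closer to the planned model. A simulation used k equal counsellors per team (k = 2 to 6, assumed), no extra counsellor variance, and a t test on counsellor means with 6k − 2 degrees of freedom.
- ICC 0.01: 0.08 (k = 2) to 0.10 (k = 6)
- ICC 0.05: 0.13 (k = 2) to 0.23 (k = 6)

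The counsellor level softens the inflation without removing it. Steps 4 to 6 describe chance differences between teams only. If teams were designated for reasons related to their practice, that would add a bias that no variance term removes.

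**The case against.** Separate teams are a reasonable choice. Brainwork includes a reorganised internal work process and team training, and one team delivering both arms would invite contamination. This stands, and it limits the point to differences that existed before the training.

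The planned model also does not ignore clustering, so 11-29% is not its error rate. That stands too; the counsellor-level figures in step 6 are the relevant ones unless the counsellor level is dropped, which the qualifier in Effect evaluation allows. Real variance between counsellors within a team would lower the inflation further.

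Four stronger readings are tempting, and the document does not support them:
- *That the teams were not drawn by lot.* The article says only that they were designated. A condensed article may omit the method, and a random choice is not ruled out.
- *That Brainwork's developers worked on an intervention team.* The article says that "professionals of one of the front offices of the Dutch SSA developed the Brainwork Intervention". It does not say that this office is one of the three in the trial.
- *That team members are stated to end the primary outcome.* Who declares fitness is not stated.
- *That team and Brainwork effects can never be told apart.* Aliasing is complete within an office, but three office pairs give slight replication (2 degrees of freedom in a paired team-level comparison). That is too little to be of much use, and it would not help against systematic selection of teams.

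**Conclusion.** The point holds as a structural limitation: arm is aliased with team within each office, neither the counsellor level nor adjustment on participants' baseline data removes a team-wide shift, and the article does not acknowledge it. The aliasing follows from the text alone.

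Its size rests on the back-solved SD, equal team sizes and an assumed ICC. On those assumptions, chance team differences have an SD of roughly a fifth (8.5/40) to just over half (22.1/40) of the target effect. Under a counsellor-level analysis the nominal 5% error becomes about 8-10% at ICC 0.01 and 13-23% at ICC 0.05. Whether the designated teams really differed beforehand is unknown, and nothing in the article shows that they did. The remedy is a cheap improvement that would let readers judge.

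**What to change.** 1. State how the two teams in each office were designated. Where teams have not yet been trained, draw lots between them. With three offices this gives only 2³ = 8 possible assignments, so it guards against selection but leaves chance differences.
2. Extract from the SSA register the sick-leave durations of workers handled by the six teams in a year before the trial, with the same 365-day cap and the same types of worker. This requires that the handling team is recorded and that team membership is broadly stable; the article documents neither.
3. Report the pre-trial arm difference with its interval, and pre-specify a sensitivity analysis giving the trial effect net of it (difference in differences).
4. Name team-arm confounding under Methodological considerations, and word the conclusion as Brainwork delivered by the designated teams.

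Cost: one extra register extract and one sensitivity analysis, with no new participants or procedures. The net estimate is less precise. If the pre-trial year also supplied 150 workers per arm (assumed), its worker-level standard error at SD 121 would be about 14.0 × √2 = 19.8 days instead of 14.0. It also relies on team differences staying stable over time.
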